### Data Management

All study data will be stored in REDCap, a secure, 21 CFR Part 11–compliant data capture system. REDCap includes automated validation checks to support data completeness and internal consistency. All data management systems used by the study team will be secured and password-protected. Upon completion of the study, all datasets will be deidentified and archived in accordance with institutional data retention policies and IRB requirements. Deidentified data may be shared for secondary analyses or replication requests, provided appropriate safeguards are in place and release is approved by the IRB.

### Confidentiality

All personally identifiable information will remain confidential and accessible only to authorized study personnel. Identifiers will be stored separately from research data and replaced with a unique study ID for analysis. Identifiable contact information will be stored securely within Stanford University systems. Video recordings and associated data will be stored on encrypted servers and destroyed at the end of the study in accordance with the approved data management plan and IRB requirements. Only deidentified data may be retained for dissemination or data sharing. No biological specimens will be collected or stored for this study.

### Statistical Methods

In this longitudinal randomized controlled trial (RCT), 90 caregiver-child dyads of children with ASD will be assessed repeatedly at baseline, weeks 4, 8, and 12, and at 4-week posttreatment follow-up, allowing for strong inference regarding the longitudinal relationships among behavioral treatment, treatment fidelity, and challenging behaviors. The core analysis strategy in this project is longitudinal mixed-effects modeling, fully using the repeatedly measured primary and secondary outcomes. For maximum likelihood estimation of mixed-effects models, Mplus will be used. Because caregivers’ fidelity in implementing the same treatment will be observed under both in-person and telehealth conditions, we will examine the mediating effect of treatment fidelity (rather than conducting per-protocol analyses). We will follow the eligibility and analytical criteria of the MacArthur approach to mediator analysis [60], which will be embedded in our mixed-effects models. Specifically, mediation will be examined through two tests: (1) whether treatment via telehealth or in person significantly increases caregiver fidelity (eligibility criterion for mediators) and (2) whether the fidelity is correlated with caregiver stress (analytical criterion for mediators). As part of the sensitivity analysis, we will also use modern causal mediation approaches that use potential outcomes and propensity scores.

We will first estimate the main effect of the intervention on our primary outcomes, the rate of child challenging behavior and caregiver stress, using standard mixed-effects modeling, fully using all available repeated measures (0-, 4-, 8-, 12-, and 16-week follow-up). The primary parameter of interest is the group difference at 12 weeks (end of treatment). We expect that children who receive telehealth-delivered SBT or in-person SBT will show significant decreases in challenging behavior compared with those who receive caregiver online psychoeducation. We further expect that caregivers who receive telehealth-delivered SBT will report significantly lower scores on the total score of the PSI-4-SF than those who receive in-person SBT.

### Protocol Deviations and Missing Data

This protocol defines a protocol deviation as any noncompliance with the clinical trial protocol, International Council for Harmonisation Good Clinical Practice, or Manual of Procedures requirements. Noncompliance may be attributable to the participant, the investigator, or the study site staff. As a result of deviations, corrective actions will be developed by the site and implemented promptly. It will be the responsibility of the site investigator to exercise continuous vigilance to identify and report deviations within 7 working days of their identification or within 14 working days of the scheduled protocol-required activity. All deviations will be addressed in the study source documents and reported to the Department of Defense program official. We will implement rigorous efforts to minimize missing data. Nonetheless, missing data may occur due to the follow-up period. Missing data due to attrition or incomplete assessments will be handled under the assumption that data are missing at random, conditional on observed information.

### Data Access and Sharing

Deidentified quantitative data (eg, caregiver survey scores and summary outcome measures) may be made available upon reasonable request and with IRB approval. Video-based material will not be publicly available to protect participant confidentiality.

### Oversight and Monitoring

The trial will be jointly coordinated by Stanford University and Behavior Change Institute. The PI ([name]) and site-PI ([name]) will provide overall scientific leadership and operational oversight, including protocol adherence, data integrity, and communication with the funding agency. A core coordinating team comprising the PI, site PI, site investigators, project coordinator, and data manager will meet regularly to review recruitment progress, data quality, and intervention fidelity.

Because this is a minimal-risk behavioral intervention with no pharmacologic or invasive procedures, a formal data safety monitoring board is not required. In accordance with Department of Defense requirements, a data and safety monitoring plan has been developed and will be implemented throughout the trial. The PI will conduct ongoing safety oversight in collaboration with the Stanford IRB and WIRB-Copernicus Group Independent Review Board (WCG IRB). All unanticipated problems, AEs, and protocol deviations will be promptly reviewed and reported in accordance with institutional and regulatory requirements.

Operational oversight will include weekly meetings among the core study team to monitor recruitment, participant progress, and protocol adherence. The full study team will meet twice weekly to review trial operations, identify emerging issues, and implement corrective actions as needed. Each site will maintain internal quality assurance procedures to ensure participant protection and accurate, complete data collection across all phases of the trial.

### Adverse Events

This protocol defines an adverse event (AE) as any event that may impact a participant’s daily activities or functioning. AEs will be graded by severity (mild, moderate, and severe), relatedness (not related, unlikely, possibly, probably, and definitely), and action taken (none, discontinued temporarily, and discontinued permanently).

All AEs will be assessed by a member of the core study team in consultation with the caregiver to determine their relationship to study procedures. AEs will be documented in REDCap and followed until resolution or stabilization. Any medical or psychiatric condition present at screening will be considered baseline and not reported as an AE unless the condition worsens during the study, in which case it will be recorded as an AE. Changes in the severity or duration of any AE will also be documented.

At each study visit, the investigator will inquire about the occurrence of AEs or serious adverse events (SAEs) since the prior visit. An SAE is defined as a life-threatening event that results in death, hospitalization, disability, or permanent damage, or requires intervention to prevent permanent impairment. SAEs may come to the attention of study personnel during visits, caregiver reports, or routine monitoring.

All AEs and SAEs will be reviewed to determine potential relevance to the study. SAEs will be reported to the Stanford IRB within 24 hours of awareness. A trained member of the study team, in consultation with the PI, will evaluate each SAE, and a complete report will be submitted to the IRB no later than 10 working days after initial notification.

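### The SAE definition joins life-threatening to the other seriousness criteria instead of listing it as an alternative, so some serious events miss the 24-hour notice and the full report

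*Protocol article*

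**What the plan says.** The Adverse Events section of the protocol article sets two tiers.

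- **AE.** The definition is broad: "This protocol defines an adverse event (AE) as any event that may impact a participant’s daily activities or functioning". AEs are graded for severity, relatedness and action taken, entered in REDCap, and followed until they resolve or stabilize.
- **SAE.** "An SAE is defined as a life-threatening event that results in death, hospitalization, disability, or permanent damage, or requires intervention to prevent permanent impairment".

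The timed reports belong to the second tier only. The first is the notice: "SAEs will be reported to the Stanford IRB within 24 hours of awareness". The second is the follow-up: "a complete report will be submitted to the IRB no later than 10 working days after initial notification".

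For events that are AEs but not SAEs, the Oversight and Monitoring section applies: "All unanticipated problems, AEs, and protocol deviations will be promptly reviewed and reported in accordance with institutional and regulatory requirements". It gives no time limit. The same section says that a data and safety monitoring plan exists under Department of Defense requirements; that plan is not shown. No other section of the article defines an SAE or lists hospitalization as a criterion in its own right.

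**The concern.** Seriousness criteria work as a list in which meeting any one is enough. Here the noun being defined is a life-threatening event, and the outcomes sit in a clause that narrows it. Staff who apply the sentence as written would ask first whether life was threatened, and would go on to the outcomes only if it was.

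The events that this wording misses are plausible in this trial. Children are enrolled because of daily or hourly self-injury or aggression. The assessment and treatment procedures present evocative conditions in the home. In the telehealth arm the clinician guides safety measures verbally. An injury could lead to admission or lasting damage without threatening life. There is no data safety monitoring board, no interim analysis for harm and no planned independent audit, so a clear rule for what counts as serious carries more weight than usual.

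What is at stake is a fixed reporting deadline and the correct classification of serious events. No estimate, power figure or significance level is affected.

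**Working it through.** No arithmetic on trial figures applies. The check is whether the sentence, on each way it can be read, catches the events it should.

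**Terms.**
- L: the event is life-threatening.
- O: it results in death, hospitalization, disability or permanent damage.
- I: it requires intervention to avert permanent impairment.

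**Readings.**
- Reading A: L and (O or I). The condition of threatening life governs everything that follows.
- Reading B: (L and O) or I. The intervention criterion stands alone.
- Alternatives: L or O or I. This is how a list of seriousness criteria is meant to work.

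| L | O | I | Reading A | Reading B | Alternatives |
|---|---|---|---|---|---|
| no | no | no | AE | AE | AE |
| no | no | yes | AE | SAE | SAE |
| no | yes | no | AE | AE | SAE |
| no | yes | yes | AE | SAE | SAE |
| yes | no | no | AE | AE | SAE |
| yes | no | yes | SAE | SAE | SAE |
| yes | yes | no | SAE | SAE | SAE |
| yes | yes | yes | SAE | SAE | SAE |

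With the criteria as alternatives, 7 of the 8 combinations are SAEs. Reading A catches 3 and misses 7 − 3 = 4. Reading B catches 5 and misses 7 − 5 = 2. These are counts of logical cases, not frequencies of events.

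Two cases are missed on both readings:

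1. A listed outcome without threat to life and without the intervention criterion (third row). In practice this means hospitalization, disability or permanent damage, since a fatal event is life-threatening by its nature.
2. A life-threatening event with none of the listed outcomes and no such intervention (fifth row).

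**What happens to a missed event.** It meets the AE definition, so it is recorded, graded, followed, and promptly reviewed and reported. It does not receive the 24-hour notice or the 10-working-day report. The severity grade does not rescue it, because the text ties neither SAE status nor the 24-hour report to a grade of severe. For comparison, the Protocol Deviations and Missing Data section gives deviations limits of 7 and 14 working days, whereas a non-serious AE has no stated limit.

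**The case against.** The strongest reply is that this is a compression slip in an article. The full protocol (version 1.9) and the data and safety monitoring plan are not shown and may list the criteria correctly. The sentence itself hints at this: a criterion about averting permanent impairment makes little sense if life must already be in danger. That is a fair account of how the wording may have arisen, but it does not remove the point. The article states a complete definition rather than leaving one out, and nothing else in it corrects the sentence.

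It can also be said that the trial limits the risk. Children whose behavior may cause moderate to severe damage requiring medical attention are excluded, evocative events are withdrawn when challenging behavior occurs, and procedures pause for safety. This stands and lowers the expected number of events, but does not make the definition right for those that occur.

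Four stronger conclusions that a reader might draw are not supported:

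- **That the SAE definition is the only route to prompt review.** It is the only one with a 24-hour clock. All AEs must be promptly reviewed and reported.
- **That every serious event short of threatening life is misclassified.** On Reading B, one that meets the intervention criterion is still an SAE.
- **That an SAE table by arm will be undercounted.** The article describes no such table. AEs are a secondary outcome, captured on a checklist of occurrence, severity and attribution.
- **That naming only the Stanford IRB in the 24-hour rule is an error because two IRBs share oversight.** It contradicts nothing, and how two boards divide reporting is operational detail that an article commonly leaves to the full protocol.

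**Conclusion.** The definition is wrong as written. On either reading, a hospitalization, disability or permanent damage that is not life-threatening and needs no intervention to avert permanent impairment is not an SAE. The same holds for a life-threatening event without a listed outcome or such intervention. The consequence is loss of the 24-hour notice and the 10-working-day report, not loss of recording, review or reporting.

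The number of events affected cannot be estimated, because the article gives no AE counts or rates. Nothing shows that any event has been handled under the literal wording. The conclusion assumes that staff apply the sentence as printed. If the monitoring plan already lists the criteria as alternatives and is what staff follow, the defect is confined to the article and the two texts need only be brought into line.

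**What to change.** 1. Reword the sentence so that any one criterion is enough. For example: an SAE is any event that results in death; is life-threatening; leads to hospitalization; causes disability or permanent damage; or needs intervention to avert permanent impairment.
2. Reconcile that wording with the data and safety monitoring plan, so that one definition governs reporting.
3. Check AEs already logged in REDCap against the corrected definition before database lock. With 81 of the planned 90 dyads enrolled by March 2026, most of the trial's AEs may already have been classified, so this step matters as much as the rewording. It is a check and does not presume that errors will be found.

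The cost is a one-sentence amendment, a single pass through the AE log, and possibly a few more SAE reports. Interventions, sample size and the efficacy analysis are unchanged.

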### Auditing

No formal or independent audits are planned due to the study’s minimal risk. The PIs and IRB will periodically review trial conduct. If required, the PI will provide direct access to all trial-related sites, source data and documents, and reports for monitoring and auditing by the funding agency and for inspection by local or regulatory authorities.

## Results

The study was funded in May 2022. Participant recruitment began in January 2024 and is projected to conclude in October 2026. As of March 2026, 81 caregiver-child dyads have been enrolled, with equal allocation across the 3 study groups (27 per group; 33%). Data analysis is expected to occur between Winter 2026 and Spring 2027, with primary results anticipated in Fall 2027.

## Discussion

### Anticipated Findings

This randomized trial directly compares telehealth and in-person delivery models to generate rigorous evidence regarding the effectiveness and feasibility of caregiver-mediated behavioral interventions for addressing challenging behaviors in children with ASD. The primary aim of this study is to determine whether caregiver-mediated behavioral treatment delivered via telehealth or in person results in greater reductions in child challenging behavior and caregiver stress compared with caregiver psychoeducation alone. We hypothesize that caregiver-mediated behavioral treatment delivered either via telehealth or in person will lead to greater reductions in child challenging behavior compared with caregiver psychoeducation alone. We also anticipate that telehealth delivery may produce comparable or greater reductions in caregiver stress relative to in-person delivery due to increased convenience, reduced logistical burden, and greater integration of intervention strategies within natural home environments.

### Comparison With Prior Work

Previous research has demonstrated that caregiver-mediated behavioral treatment can effectively reduce challenging behavior in children with ASD and improve caregiver outcomes. Telehealth delivery models have shown promise in increasing accessibility and reducing barriers to treatment, particularly for families in rural or underserved regions. However, few studies have directly compared telehealth and in-person delivery models for behavioral interventions targeting challenging behavior within randomized designs. This study builds on prior work by evaluating these delivery modalities within a rigorous randomized framework while incorporating community-informed outcomes that reflect the priorities of families and payers.

Beyond the scientific literature, there is a critical need for data that help families, providers, and payers make informed decisions about behavioral care for children with ASD. Insurance partners from our community advisory board have noted that the limited number of RCTs and comparative effectiveness research remains a barrier to broader coverage of telehealth-delivered ABA services. Reflecting the priorities of our ASD community advisory board, this trial prioritizes outcomes, such as caregiver stress and family quality of life, that extend beyond clinical symptom reduction to capture the broader impact of intervention on families.

### Strengths and Limitations

This study has several strengths. First, the RCT design provides a rigorous method for evaluating the comparative effectiveness of telehealth and in-person caregiver-mediated behavioral treatment. Second, the study incorporates community engagement throughout the design process, ensuring that the outcomes assessed reflect priorities identified by caregivers, clinicians, and payer representatives. Third, the intervention is delivered in the family home environment, increasing ecological validity and supporting the development of sustainable caregiver-implemented strategies.

Several limitations should also be acknowledged. This study is conducted at a single research site, which may limit the generalizability of the findings to other clinical settings or service delivery systems. In addition, participation is limited to English-speaking caregivers, which may reduce the applicability of findings to linguistically diverse populations. Additionally, the study excludes children who engage in the most severe forms of dangerous behavior that may require medical intervention or intensive clinical supervision. As a result, the findings may not fully generalize to families of children with the highest levels of behavioral risk, who may require more intensive or specialized services.

### Future Directions and Conclusions

If the intervention demonstrates positive outcomes, future research could extend this model toward tiered service-delivery approaches that integrate both caregiver-mediated and provider-delivered ABA treatment. Such frameworks could expand access to evidence-based care while reducing costs and family burden, aligning with modern standards of trauma-informed, family-centered behavioral health. Ultimately, this project aims to generate high-quality evidence supporting the responsible and equitable expansion of telehealth services for families of children with ASD. Future studies may also examine strategies to adapt and extend telehealth-delivered caregiver coaching models to linguistically diverse populations, and to children with more complex or severe behavioral presentations. In addition, future research may evaluate the long-term sustainability of caregiver-mediated interventions and their impact on service utilization, cost of care, and family well-being.

Although many funders now cover telehealth [61], the continued expansion of these services will be strengthened by rigorous, controlled evidence demonstrating clinical effectiveness and family benefit. This trial will provide comparative effectiveness data that may inform payer policy, clinical decision-making, and equitable service delivery. In addition, by empowering caregivers as primary agents of change within natural home environments, this model may support more sustainable, long-term behavioral solutions, particularly for families in underserved regions and those encountering systemic barriers to timely care.

### Dissemination Plan

Upon the successful completion of this clinical trial, the treatment manual will be made publicly available on the study website to support the dissemination of compassionate, trauma-informed SBT procedures. Study findings will be disseminated through peer-reviewed publications and presentations at national and international conferences focused on ASD research and behavioral health. Authorship eligibility will be determined in accordance with the International Committee of Medical Journal Editors guidelines. Results will also be shared with community partners and caregiver organizations to support the translation of findings into practice.
